### Aims

This study represents the third, and last, phase (pilot 3) of large-scale pilots aiming to gradually co-design and iteratively test the PC4L integrated platform and modules.

While pilot phases 1 and 2 focused on technical feasibility and patients’ satisfaction, this protocol focuses on the following objectives:

To assess the impact of using the PC4L platform on patients’ quality of lifeTo compare the metrics generated by the PC4L platform in real-life conditions with the clinical outcome measuresTo evaluate the feasibility and safety of measuring disease progression and patient health status through the global functioning of the PC4L systemTo assess and compare the feasibility and usability of 2 different versions of the PC4L system (fully equipped version vs cloud-based solution)To increase patients’ safety and empowerment

As the primary outcome, the study will provide:

The difference in quality of life between groups (experimental vs control group), measured by the EQ-5D-3L scale at the end of the study

The following secondary outcomes will also be acquired:

The correlation coefficient of the PC4L platform metrics (eg, steps and physical activity levels, sleep, number of falls, cognitive scores) with the clinical outcome measures (eg, motor clinical evaluation, sleep questionnaire, Falls Efficacy Scale-International [FES-I], cognitive evaluations) measured at baseline, end of the study, and the values of change from baselineSystem usability assessment, measured through the System Usability Scale (SUS), at the end of the studyUsers’ satisfaction with the PC4L system, measured through a 5-point Likert Scale, the mHealth User Satisfaction Questionnaire, and the participants’ answers to open questions, at the end of the studyChanges in patients’ satisfaction and empowerment, measured by the Patient Assessment of Chronic Illness Care (PACIC) and the Short Assessment of Patient Satisfaction (SAPS) scales, respectively, at baseline and at the end of the studyChange in patients’ use of medical resources (number of admissions and number of days spent in health institutions) in the last month, measured at baseline and at the end of the study

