#### PC4L Mobile App

The PC4L app includes a prescription dashboard, which monitors drug compliance; questionnaires on health status and physical activity, to be filled periodically; a symptom diary, which registers the symptoms experienced by the patient (ie, falls, freezing, loss of balance); physical activity recommendations; and daily personalized notifications on physical activity, hydration, and nutrition.

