#### Metrics

During the monitoring period, specific metrics (Table 1) are collected, continuously and passively, through the PC4L system.

**Table 1 table1:** Metrics and related devices used during patients’ monitoring.

Metrics	Devices
Walking parameters	Wristband and phone
Bradykinesia	Wristband and phone
Loss of balance	Cameras
Falls	Cameras and wristband
Festination	Wristband and phone and camera
Physical activity	Wristband
Freezing	Wristband and phone and camera
Inactivity	Wristband
Compliance with medication	App
Sleeping pattern	Wristband
Interaction patterns with the devices	Platform or app
Usage of the physical activity recommendation services	Number of clicks per week of the different services

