### Study Design

A prospective multicenter clinical study is conducted in 5 European countries: Germany, Italy, Portugal, Romania, and Spain (also including 6 pilot centers).

The pilot sites are (1) Asociacion Parkinson Madrid (APM), Madrid (Spain); (2) Casa di Cura del Policlinico (CCP), Milano (Italy); (3) Campus Neurológico Sénior (CNS), Lisbon (Portugal); (4) University and Emergency Hospital of Bucharest (UHB), Bucharest (Romania); (5) University of Medicine and Pharmacy (UMF), Bucharest (Romania); and (6) Wohlfahrtswerk für Baden-Württemberg (WBW), Stuttgart (Germany).

There are also 3 different scenarios: (1) rehabilitation center (inpatients and outpatients); (2) day care centers; and (3) home set (ie, patients’ home).

The duration per patient, at home and in the day care center, will be up to 3 months. Participants in the rehabilitation center participated during the period of their stay in the center (not exceeding the 3 months).

A specific route diagram is presented in Figure 2 in accordance with the CONSORT (Consolidated Standards of Reporting Trials) guidelines. The protocol of this study was developed in accordance with the SPIRIT (Standard Protocol Items: Recommendations for Interventional Trials) guidelines (Figure 3) [12]. The schedule of enrollment, interventions, and assessments is presented in Figure 3.

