### Randomization

Patients were randomized in a ratio of 1:1 to the intervention group (use the PC4L system) or the control group (no intervention) by an independent, nonclinical partner of the project consortium.

Patients allocated in the intervention group were randomized in a ratio of 3:1 to the “cloud-based solution” and the “fully equipped” PC4L system version.

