#### Intervention Group

The patients recruited and assigned to the experimental group received specific instruction in using the project platform, but without any specific program concerning the activities.

Specifically, patients, after the baseline assessment, received the instrumental setup and indications on its functionalities. Patients were instructed about the use of the Fitbit, the PC4L app, and the cognitive games on a tablet or computer. Patients were also provided with manuals.

Specifically, according to the study approach detailed by Biehl et al [9], the patients were instructed to complete the following questionnaires in the app during the first week and during the last week of the study period: the 10-item Eating Assessment Tool (EAT10) [13] for evaluation of dysphagia; the Edmonton Symptom Assessment System (ESAS) [14] and the Patient Global Impression (PGI)—Severity [15] for evaluation of symptoms; and the International Physical Activity Questionnaire (IPAQ) [16] for evaluation of physical activity. In addition, during the last week of using the app, patients were requested to complete the SUS [17], via the app, for evaluation of usability.

The platform was installed in each scenario with the assistance of the project research staff (ie, bioengineers).

A total of 2 versions of PC4L systems were installed: while the cloud-based system (which only required a smartphone and a wearable sensor) was used in all scenarios, a fully equipped version was implemented only in the rehabilitation scenario.

The patients received the same directions in all 3 scenarios.

At the end of the study period, patients performed end-of-study evaluations and returned the instrumental setup.

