### Study Assessments

In-person assessments took place at baseline and at the end of the study (3 months follow-up or at discharge from the rehabilitation program).

Specifically, the sample characterization and clinical evaluation of the participants (both experimental and control group patients) were performed at baseline. The clinical evaluation with specific tests and scales was repeated at the end of the study.

At the beginning and at the end of the study, all patients were assessed on quality of life through a specific scale (EQ-5D-3L).

Only for patients assigned to the intervention group, their experience with the PC4L platform was assessed in terms of usability at the end of the experimental period.

Figure 3 and the “Data Collection and Analysis” section report specific outcomes that will be used.

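### The plan correlates platform metrics with clinical measures at baseline and as change from baseline, but devices are issued only after the baseline assessment, so no pre-intervention metric can exist

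*Protocol article*

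**What the plan says.** The first secondary outcome under Aims is "The correlation coefficient of the PC4L platform metrics (eg, steps and physical activity levels, sleep, number of falls, cognitive scores") with clinical measures such as the motor evaluation, the sleep questionnaire, the FES-I and cognitive evaluations. Its time points are "measured at baseline, end of the study, and the values of change from" baseline. Under Statistical Analysis, these Pearson and Spearman correlations serve to validate the platform metrics.

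Other sections fix the order of events:

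- Study Assessments: "In-person assessments took place at baseline and at the end of the study".
- Intervention Group: "patients, after the baseline assessment, received the instrumental setup and indications on its functionalities".
- Metrics: "During the monitoring period, specific metrics (Table 1) are collected, continuously and passively, through the PC4L system".
- Randomization: "Patients were randomized in a ratio of 1:1 to the intervention group (use the PC4L system) or the control group (no intervention").
- PC4L Mobile App: the app sends "daily personalized notifications on physical activity, hydration, and nutrition", along with physical activity recommendations.
- Study Design: "Participants in the rehabilitation center participated during the period of their stay in the center (not exceeding the 3 months"). Home and day care follow-up is up to 3 months.

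**The concern.** The outcome names a time point at which the metrics cannot have been recorded. The clinical scales have a true pre-intervention baseline and the metrics do not. The measuring instrument is also the treatment: the app that accompanies the wristband prompts physical activity from the time it is in use, and steps and activity are among the metrics to be validated.

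Two things follow. The correlation labelled baseline pairs a scale scored before the intervention with a metric recorded during it. The correlation of changes pairs two differences over different periods, because any early response to PC4L is contained in the clinical change but wholly or partly absent from the metric change. What is at stake is how the validation result is described and, for the change correlation, whether a weak coefficient would reflect a poor metric or mismatched periods.

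**Working it through.** The plan gives no figure for this point, so the check compares the sections and then asks what the mismatch does to a correlation coefficient.

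**1. Can a baseline metric exist?**
- The clinical baseline is scored before the devices are handed over (Intervention Group).
- Metrics come only through the PC4L system, during monitoring (Metrics).
- Controls do not use the system (Randomization; Control Group).
- No wear period, run-in or silent recording before device issue is described anywhere.

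Pre-intervention metric values available: 0 of 279 intervention patients.

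**2. What does each change score cover?**
- Clinical change: from before the intervention to the end of the study.
- Metric change: from some point after device issue to the end of the study.

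**3. Does the missing early part alter the correlation?** Let C be the clinical change, M the full metric change, and kM the part that remains when the early period is lost. If k is the same positive number for everyone, corr(kM, C) = corr(M, C), for Pearson and Spearman alike. If 25%, 50% or 75% of every patient's response had already occurred in the early window, 75%, 50% or 25% of it would remain in the change score, and the coefficient would be the same in all three cases. Distortion requires k to vary between patients.

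**4. Can k vary?** Yes, through differing early response or differing follow-up. To illustrate the second, assume linear change and one-week averaging windows at each end of a follow-up of T weeks. Neither assumption is in the protocol. The first-week mean lies at 0.5/T of the full change and the last-week mean at (T − 0.5)/T, so

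k = (T − 0.5)/T − 0.5/T = (T − 1)/T.

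| T (weeks) | k |
|---|---|
| 13 | 12/13 = 0.92 |
| 8 | 7/8 = 0.88 |
| 4 | 3/4 = 0.75 |
| 2 | 1/2 = 0.50 |

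Below 2 weeks (7 + 7 = 14 days) the two windows would overlap. Under these assumptions, a patient followed for 4 weeks with a full change of 1 unit is recorded as 0.75. A patient followed for 13 weeks is recorded above that with any full change over 0.75 × 13/12 = 0.81 units. Ranks can therefore swap between patients with different lengths of stay.

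**5. How many patients could be concerned?** Table 2 of the protocol places 204 of 558 participants in rehabilitation (37%) and 82 + 272 = 354 in day care or at home. These counts cover both arms. Lengths of stay are not reported, so step 4 shows a range of possibilities and is not an estimate.

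**The case against.** **The Aims sentence is ambiguous.** The time points may qualify only the clinical measures, which directly precede them and which are indeed taken at baseline and at the end. This reading is fair, but it does not remove the problem: a correlation with baseline scores, or with change from baseline, must still use metrics recorded after device issue.

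**Window definition belongs in an analysis plan.** It does, and the absence of a window is not the point here. An unseen plan could choose the days, but it could not supply data from before the devices were issued.

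**Early-use metrics can still validate.** This stands for the cross-sectional correlation. No delay between assessment and device issue is stated, and scales scored shortly before device issue may agree well with metrics from the first days.

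**The effect may be small.** This also stands in part. A uniform loss does nothing to the coefficient, and with linear change over about 13 weeks some 92% of the change is retained.

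**Stronger inferences are tempting but unsupported.** A reader might infer that short rehabilitation stays make the early and late windows overlap. The document gives only an upper limit on stay, and its first-week and last-week schedule is for in-app questionnaires, not sensor metrics. A reader might also infer that the daily notifications target sleep. The app section lists physical activity, hydration and nutrition; sleep appears only among the recommendation areas of the Decision Support System.

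**Conclusion.** The labelling conflict is established by the text: the metric part of this outcome cannot be delivered at baseline or as change from a pre-intervention baseline for any of the 279 intervention patients. This assumes that the sequence in the Intervention Group section was followed and that no undescribed recording period took place.

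Distortion of the change correlation is plausible but not quantified. It depends on early response or follow-up length differing between patients. Rehabilitation follow-up that equals length of stay makes such differences likely, but the document gives nothing from which to derive their size.

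A reader might go further and conclude that the change correlation must be weakened by some fixed share, or that the validation as a whole fails. The document supports neither. A fixed share cancels out of the coefficient, the early cross-sectional correlation can still inform if correctly labelled, and the end-of-study correlation is unaffected. Nor does the point undermine the third objective as written, which concerns the feasibility and safety of measuring progression. It affects a secondary outcome in one arm; the EQ-5D-3L comparison is untouched. It merits correction because it changes what the trial may claim and costs almost nothing to put right.

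**What to change.** Reconcile the Aims section with the Intervention Group section:

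- Rename the metric time point as early use (first 7 worn days, on intervention), and the metric change as change during use. Do not describe either as referring to a pre-intervention baseline.
- For the end-of-study correlation, use the last 7 worn days before the final assessment, and rest the validation claim mainly on this result.
- Compute the correlation of changes only in patients whose early and late windows do not overlap, and state that the clinical and metric changes cover different periods.
- If a recording period without recommendations did take place before the intervention became active, describe it and use it instead.

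The cost is a change of wording and a rule for extracting metrics from data that the platform collects continuously. Enrollment is closed and no new data are needed. The downside is small: any patients with very short stays leave the change analysis.

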### Recruitment

Patients with PD and other parkinsonian syndromes, AD, or ODs were invited to participate from the clinical centers involved in the study. Each participant organization was assigned to recruit a number of participants related to their skills, experience, number of researchers involved, and access to users (Table 2).

**Table 2 table2:** Distribution of participants per clinical center and scenario.

Scenario/clinical center	Rehabilitation (n=204), n	Day care (n=82), n	Home (n=272), n	Total (N=558), n
APM^a^	80	N/A^b^	26	106
CCP^c^	63	N/A	62	125
CNS^d^	46	N/A	86	132
UHB^e^	15	N/A	15	30
UMF^f^	N/A	30	30	60
WBW^g^	N/A	52	53	105

^a^APM: Asociacion Parkinson Madrid.

^b^N/A: not applicable.

^c^CCP: Casa di Cura del Policlinico.

^d^CNS: Campus Neurológico Sénior.

^e^UHB: University and Emergency Hospital of Bucharest.

^f^UMF: University of Medicine and Pharmacy.

^g^WBW: Wohlfahrtswerk für Baden-Württemberg.

To reach the planned number of recruits, many strategies were implemented: participants were contacted through online webinars; through brochures placed in specific centers such as pharmacies, leisure centers, and medical offices; and through patients’ associations. Further, regular updates were posted via online newsletters on different websites, such as the PC4L website and end users organizations’ websites. In addition, information about the PC4L pilot 3 study was shared during national and international conferences. Recruitment was also promoted in a collaborative way thanks to partners from other European projects. Finally, participants were recruited in person when accessing the medical facilities and via phone contact or emails after searching local databases.

Patients who discontinue the study participation because of medical conditions (ie, infections, falls, medical emergencies) or unwilling to participate any longer for other reasons (ie, difficulty with technology, loss of interest) will be considered dropouts.

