### Data Collection and Analysis

#### Clinical Assessment

Evaluators (ie, medical doctor, physical therapist, and neuropsychologist), at the beginning and at the end of the study, conducted the following clinical evaluation scales and tests:

The Movement Disorder Society-Unified Parkinson Disease Rating Scale (MDS-UPDRS) [18] will be used to objectively quantify the motor and nonmotor aspects of PD. Changes in the MDS-UPDRS score will be investigated, with higher scores meaning worse outcomeThe Clinical Dementia Rating Scale (CDRS) [19] will be used to assess the cognitive status of AD and OD. It yields a single score on a scale of 0-5, with higher scores indicating worse outcome. Change in the CDRS score will be measured at baseline and at the end of the studyThe FES-I will be used to evaluate the subjective fear of falling of the patients. It yields a single score on a scale of 16-64, with higher scores indicating worse outcomeThe Pittsburgh Sleep Quality Index (PSQI) [20] will be used to evaluate the quality of sleep. Change in the PSQI score will be measured at baseline and at the end of the study. It yields a single score on a scale of 0-21, where higher scores mean worse outcomeThe State-Trait-Anxiety-Inventory (STAI) [21] will be used to assess the anxiety status (trait and state). Change in the STAI score will be measured at baseline and at the end of the study. It yields a single score on a scale of 20-80, where higher scores mean worse outcomePresence of festination, dysphasia, wandering episodes, and nonprogrammed medical resources use in the last month will be assessed (eg, access to emergency room)The Barthel Index (BI) is an ordinal scale used to measure performance in activities of daily living (ADLs) [22]. Each performance item is rated with a given number of points assigned to each level or ranking. It uses 10 variables describing ADL and mobility and yields a single score on a scale of 0-100, where higher scores mean better outcomeThe PACIC will be used to determine the involvement of the patient in his/her care plan. Change in the PACIC score will be measured at baseline and at the end of the study. It yields a single score on a scale of 0-5, where higher scores mean better outcomeSimilarly, the SAPS was used to evaluate the user’s satisfaction with respect to the medical treatment received. Change in the SAPS score will be measured at baseline and at the end of the study. It yields a single score on a scale of 0-28, where higher scores mean better outcomeThe Cumulative Illness Rating Scale-Geriatric (CIRS-G) [23] is used to include the presence of comorbidities in the clinical profile. Change in the CIRS-G score will be measured at baseline and at the end of the study. It yields a single score on a scale of 0-56, where higher scores mean worse outcome

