### Statistical Analysis

Descriptive analysis will be performed for all variables to characterize the sample. For continuous variables, mean, SD, median, and range values will be calculated. For categorical variables, absolute and relative frequencies will be used to describe the data [29-31].

Normality will be studied using the Kolmogorov-Smirnov and Shapiro-Wilk tests. The effect of using the PC4L system will be analyzed by applying the paired-sample *t* test (2-tailed) and the Wilcoxon signed rank test to each variable (statistical significance will be set at P<.05).

The Pearson and Spearman correlation tests will be used to validate the PC4L systems metrics (statistical significance will be set at P<.05).

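### The medical-resource outcome is defined two ways, and the broader definition would count the scheduled stay of rehabilitation inpatients

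*Protocol article*

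**What the plan says.** The Aims section lists, among the secondary outcomes, how much health care patients received, as a change from the first to the final assessment, counted as "number of admissions and number of days spent in health institutions) in the last month". It does not separate planned from unplanned use and does not say how the rehabilitation stay is handled.

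The Clinical Assessment section returns to resource use in a list item on the presence of certain symptoms and events: "nonprogrammed medical resources use in the last month will be assessed (eg, access to emergency room". The look-back is the same, but the scope is narrower and no count of admissions or days is mentioned.

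Three other statements bear on the point:

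- Study Design describes one scenario as "rehabilitation center (inpatients and outpatients" and adds: "Participants in the rehabilitation center participated during the period of their stay in the center (not exceeding the 3 months".
- Study Assessments places the final assessment at "3 months follow-up or at discharge from the rehabilitation program".
- Statistical Analysis says the effect of the system will be examined by the "paired-sample *t* test (2-tailed) and the Wilcoxon signed rank test to each variable".

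**The concern.** One outcome should have one definition, and here the choice changes the result. A scheduled rehabilitation stay counts as institution days under the Aims wording and does not count under the Clinical Assessment wording. An inpatient assessed at discharge has, by design, spent the days just before that assessment in an institution. If those days are counted, the change from baseline partly measures the setting in which the patient was recruited and not the effect of PC4L.

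The form matters too. A record of whether nonprogrammed use occurred does not yield numbers of admissions or days. If the Clinical Assessment item is the operational form of the outcome, it does not, as worded, deliver what the Aims section promises. If it is a separate item, the article does not say how the Aims outcome is collected.

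The abstract and the Results section both name use of medical resources among the things the trial will report on, so the definition should be settled before analysis.

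**Working it through.** **No figure to reproduce.** The article attaches no number to this outcome. Its only design calculation is the sample size for the EQ-5D-3L, which this point does not touch.

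**Step 1: the two definitions side by side.**

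| | Aims | Clinical Assessment |
|---|---|---|
| Scope | Not restricted | Nonprogrammed use only |
| Form | Counts of admissions and of days | Listed under presence; emergency access as example |
| Look-back | Last month | Last month |
| Index rehabilitation stay | Not mentioned | Excluded by implication, being programmed |

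**Step 2: how many participants could be affected.** Table 2 in the Recruitment section gives 80 + 63 + 46 + 15 = 204 rehabilitation participants, and 204/558 = 36.6%. This is an upper bound, because the scenario includes outpatients and the split is not given. Home and day care participants have no rehabilitation stay as part of their scenario.

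**Step 3: size of the shift under the literal Aims wording.** Let p be the inpatient share of the 204, L the stay days inside the end-of-study month, and b the stay days inside the baseline month. The mean change produced by the stay alone, over all participants, is

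(204/558) × p × (L − b).

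The article gives none of p, L or b. Assumed ranges are p from 0.25 to 1 and L from 14 to 30, with b = 0.

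- Low end: among rehabilitation participants 0.25 × 14 = 3.5 days; over all 558, 0.3656 × 3.5 = 1.3 days.
- Middle: 0.5 × 21 = 10.5 days; over all 558, 0.3656 × 10.5 = 3.8 days.
- High end: 1 × 30 = 30 days; over all 558, 0.3656 × 30 = 11.0 days.

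If some of the stay falls before the baseline assessment, b is above zero and the shift shrinks. At b = L it vanishes. Under the nonprogrammed definition it is zero throughout.

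**Step 4: effect on each type of analysis.** A within-arm paired test takes the Step 3 shift directly into its estimate. With 1:1 allocation the expected shift is the same in both arms and cancels in a between-arm difference, unless length of stay differs by arm. What remains is variance. For p = 0.5, the affected fraction is q = 0.3656 × 0.5 = 0.183, and the SD contributed by the stay is L × √(0.183 × 0.817) = 0.3865 L. With 279 per arm, the stay's own contribution to the 95% half-width is 1.96 × 0.3865 L × √(2/279):

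- L = 14: SD 5.4 days, half-width 0.9 days.
- L = 30: SD 11.6 days, half-width 1.9 days.

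**Step 5: the window for short stays.** If a participant is in the study for T days and T is under 30, a 30-day look-back at the end reaches 30 − T days before baseline and overlaps the baseline window. For example, T = 14 gives 16 overlapping days. The article gives no stay lengths, so how often this happens is unknown.

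**The case against.** The best defence is that the two sections can be read together: the Aims section names the units and the Clinical Assessment section names the kind of use, over the same one-month window. On that reading the scheduled stay is never recorded and the problem disappears. This is a possible reading, and the Aims section does not say that every admission counts. But the article does not state it, and it leaves unexplained how an item listed under presence produces counts of admissions and days. The need to reconcile the sections stands.

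The other main objection is that randomisation protects the comparison. This is correct for a between-arm analysis, as Step 4 shows. It does not help the paired tests that the article names. The use of within-arm tests is a wider issue affecting other outcomes, but it is what turns this ambiguity into an apparent effect. The same test in the control arm would be expected to show the same rise.

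A reader might go further in three ways that the documents do not support:

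- **That the stay is certainly counted and swamps any PC4L effect.** The Aims section is silent on the stay, and no expected effect on resource use is given to compare it with.
- **That a large paired test statistic proves a large bias.** If the stay is the only source of variation, z = √(279 × q/(1 − q)), which is 7.9 at q = 0.183 whatever the number of days. It says nothing about the size of the shift.
- **That the one-month look-back is an error because it misses the first two months of a 3-month follow-up.** Equal look-backs at both assessments are a legitimate design choice. Only the overlap for stays under a month needs a note.

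**Conclusion.** The inconsistency is on the page: one section defines unrestricted counts and days, the other the presence of nonprogrammed use, and nothing reconciles them. The consequence is conditional. If the Aims wording is applied literally, the scheduled stay of inpatients assessed at discharge enters the outcome. It then adds noise between arms and appears as a change within arms. If the nonprogrammed restriction applies, nothing is added.

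The range of about 1.3 to 11 days is illustrative. It rests on an assumed inpatient share, assumed stay days in the final month, and no stay days in the baseline month. The point concerns one secondary outcome and has no bearing on the primary outcome or the sample size. It should be corrected before that outcome is analysed.

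**What to change.** Use one definition in the Aims and Clinical Assessment sections: nonprogrammed admissions, the days they led to, and emergency visits. State that the index rehabilitation stay is excluded. Compare the outcome between the randomised arms and do not rest the effect on within-arm paired tests. Note that for stays under one month the end-of-study window overlaps the baseline window. If the case report form recorded only whether nonprogrammed use occurred, describe and analyse the outcome as a yes/no variable.

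This costs a few lines of protocol and analysis text. Enrolment ended in February 2023, participation lasts at most 3 months and the article appeared in July 2023, so the follow-up question can probably no longer be changed. The definition and the analysis still can. The downside is that planned use is no longer captured in this outcome; if it is of interest, it should be reported separately.
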